## Methods

### Study design

We aim to recruit 864 primary caregivers of children aged 2 to 9 years old from North Macedonia, Romania (both classified as upper middle-income countries; the World Bank categorised Romania as high-income country based on 2019 per capita income for the first time) and Republic of Moldova (lower middle-income country; *n* = 288 per country). Participants will be randomly allocated to one of the two parallel study arms: control group (consisting of a lecture) or a parenting intervention group receiving a five-session PLH-YC programme.

#### Recruitment

Recruitment of participants and baseline assessments are scheduled to take place from December 2020 to February 2021 in all three countries, a timeline which loosely corresponds to the middle of the 2020/2021 school year. However, the COVID-19 pandemic might cause some variation as study teams follow national policies and timelines regarding the new school year and access to schools.

Potential participants will be referred to the study by school counsellors, teachers and educators, or community workers. Additionally, all countries will advertise and provide study information on relevant websites and social media pages. On first contact with the research team, parents will be assessed for eligibility, and scheduled for providing informed consent and pre-assessment data. After the baseline assessment, they will be randomly allocated to one of the study conditions. During the recruitment stage, we will encourage secondary caregivers (i.e. fathers, grandparents, social tutors) to enrol for assessment and to take part in the programme, alongside primary caregivers.

### Participants and eligibility criteria

Potential parents or other primary caregivers will have the following inclusion criteria: (a) be aged 18 years or older, (b) be responsible for the care of a child between the ages of 2 and 9; (c) report at least subclinical levels of child’s behavioural problems as assessed with the oppositional defiant disorder subscale (ODD) of the Child and Adolescent Behavior Inventory (CABI, scores ≥ 10 will be included) [41, 42]; (d) have spent at least four nights a week with the child in the same household during the previous month and will continue to do; (e) agree to being randomised to one of the conditions; (f) consent to participate in the full study; (g) have adequate language skills to participate in the group /lecture, either in the primary language of the group or with additional language support provided. We will exclude primary caregivers whose children have been removed from their custody.

Inclusion criteria for facilitators are as follows: 1) aged 18 or older, 2) prior participation in a training workshop for the lecture/PLH-YC, 3) agreement to either deliver the lecture (one session) or PLH-YC (five sessions), 4) provision of consent to participate in the full study.

#### Group allocation and allocation concealment

Prior to randomisation, all countries will identify and select a sample of recruitment sites (schools, kindergartens, community, and social services centres) covering different neighbourhoods, geographical areas, ethnic compositions, and socio-economic strata in and around Skopje (North Macedonia), Cluj-Napoca (Romania), and Chișinău (Republic of Moldova).

Randomisation will be coordinated by one of the project partners (University of Klagenfurt) using an online randomiser, https://www.randomizer.org/ (*N* = 288 per country, 864 in total). Participant numbers will be randomised to the PLH-YC programme or the control condition after completion of the baseline assessment based on the randomisation list (individual 1:1 randomisation in blocks of 24). The randomisation list will be provided to the team in Bremen, who will be contacted after each participant is enrolled to unveil their assignment. This threefold procedure allows the analysis team to remain blind to group assignment, ensures that assignment occurs independently and ensures that teams in each country receive allocation information after enrolment.

Participants will be allocated to groups after completion of the pre-assessment. Thus, outcome assessors and participants will be blinded to group allocation at pre-assessment. All data assessors conducting pre-test, periodic, post-test, and follow-up interviews with parents will be blinded regarding the allocation of participants to the groups to minimise evaluation bias: The implementation of the intervention will be conducted by different staff (programme coordinators and facilitators) than the assessments. Thus, data assessors will be unaware of the group allocation of participants at the later assessment points (periodic, post, follow-up). To ensure that participants do not reveal their group allocation during the post- and follow-up assessment to the assessor, the data assessor will ask the participants to not share the group allocation at the beginning of the interview. Only in cases where the parent reports a (serious) adverse event, will the group allocation be unblinded (during periodic  and follow-up assessments). Upon completion of the pre-test measurements, caregivers will be notified of their allocation status.

Although one-to-one randomisation will be used, this will done in blocks of 24 (12 control and 12 PLH-YC) and vary in implementation for Republic of Moldova compared to Romania and North Macedonia. In the Republic of Moldova, participants within each of the 12 recruitment sites will be randomly allocated to either the control or the intervention due to the geographical spread of the sites across the country. In Romania and North Macedonia, participants will be assigned to any PLH-YC programme or any control lecture group and not based on region, but rather based on scheduling availability.

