If restrictions due to the COVID-19 pandemic will not allow in-person assessments, interviews will be completed over the phone. Because parents will not have the option to answer items privately over the phone, the sensitive items will not be administered during phone assessments. If restrictions due to the COVID-19 pandemic do not allow in-person assessments at post-test and follow-up assessment, parts of the assessment will also be offered online (the sensitive items) so that parents may answer the sensitive items privately via the online survey. If sensitive baseline measures (parents’ own history of child maltreatment) cannot be administered during the pre-assessment (due to phone assessment mode), they will be assessed at the next possible assessment point (e.g. post-assessment).

Approximately 4 months after the pre-assessment, post-test assessments will be carried out with the help of the same research assistants, blinded to the study conditions (planned for May / June 2021). Around 12 months after pre-assessments, we plan to carry out the follow-up assessment (December 2021–February 2022).

Three repeated ratings of child and parent behaviour in the past 24 h will be assessed over the phone between pre-intervention and post-assessment. For the PLH-YC group, after the 1st, 3rd, and 5th session (lecture: after the lecture, 2 weeks and 4 weeks later), research staff will phone participants in order to monitor the adverse events and to assess parent and child behaviour, see Fig. 1Appendix 2—Study flowchart, for a tentative timeline and Additional file 1—Schedule of enrolment, interventions and assessments (SPIRIT Figure).

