#### Adverse event assessment procedure

Information about adverse events (AE) will be collected throughout trial implementation (at pre-test and at follow-up, as well as during the three phone assessments between pre-and post-assessment at the same time as administering the PDR). With a standardised checklist (12 items), newly occurred or worsened physical/medical problems (three items; e.g. accident), behavioural problems (three items; e.g. aggressive/violent behaviours), emotional problems (one item), and other significant problems in daily life (five items, e.g. unplanned hospitalisation) will be collected as well as the subjective ratings of their severity (1 = mild, 4 = severe; answer format significant problems in daily life: happened: yes/no). If an AE with a severity of ≥ 3 or a significant problem in daily life is reported, a follow-up questionnaire will be completed in order to get a better understanding of what happened (e.g. detailed description of the event and actions taken, outcome, happened to child/caregiver). Based on the participant’s report, the research teams will aim to classify the magnitude of the AE as well as the likelihood that it is related to the project. Serious adverse events (SAE) will be reported to the local ethical boards as well as to the Data Safety and Monitoring Board (DSMB) and the central institutional review board (IRB) in Klagenfurt. The DSMB is independent from the consortium or the funding body and comprises two senior researchers with specialisation in parenting programmes, child development and child mental health who regularly review study protocol amendments, data collection and implementation procedures, participant safety, and study ethical aspects. The DSMB is notified immediately with regard to SAE occurrence, study misconduct, or other breaches in ethics and is responsible for the decision to continue, amend, or stop the trial immediately.

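### The adverse-event exception can end assessor blinding before later outcome interviews, on a trigger that partly overlaps the primary outcome, and the article's blinding statements do not allow for it

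*Protocol article*

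**What the plan says.** Three sections of the Protocol article bear on this.

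*Group allocation and allocation concealment* promises blinding without reservation: "All data assessors conducting pre-test, periodic, post-test, and follow-up interviews with parents will be blinded regarding the allocation of participants". It repeats that "data assessors will be unaware of the group allocation of participants at the later assessment points (periodic, post, follow-up" and rests this on delivery and assessment being done by different people. The same paragraph then states the exception: "Only in cases where the parent reports a (serious) adverse event, will the group allocation be unblinded", and places it at the periodic and follow-up assessments.

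*Adverse event assessment procedure* collects events at baseline, at follow-up and "during the three phone assessments between pre-and post-assessment at the same time as administering the PDR". The 12-item checklist covers new or worsening problems. It includes "behavioural problems (three items; e.g. aggressive/violent behaviours", three physical or medical items, and "emotional problems (one item), and other significant problems in daily life (five items, e.g. unplanned hospitalisation".

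*Procedure* says of the calls that "research staff will phone participants in order to monitor the adverse events and to assess parent and child behaviour", and of the four-month visit that "post-test assessments will be carried out with the help of the same research assistants, blinded to the study conditions".

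**The concern.** The exception operates before the outcome interviews that the blinding is meant to protect, and its trigger is not independent of the outcome. A parent who reports worsening aggression in a call reports something close to what the trial measures. If that report reveals the arm to the person who next rates or interviews the family, blinding fails partly according to how the child is doing. The adverse-event profile could also differ between arms, in which case the loss would be unequal.

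Two things are at stake: the credibility of the assessor-dependent primary measures, and the truth of the statement that post-test assessors were blinded.

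**Working it through.** The plan states no figure here and gives no event or unblinding rate, so the check is a comparison of the text.

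1. **Order in time.** The sequence is baseline, three calls, post-test at about 4 months, follow-up at about 12 months. The exception covers the calls, so it can operate on up to three occasions before post-test. Unblinding at the first call precedes the PDR ratings at the second and third.

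2. **Who interviews.** The allocation section lists periodic interviews with post-test and follow-up ones as the work of the data assessors. *Procedure* opens by assigning in-person and telephone interviews to trained data assessors. Callers and post-test interviewers are therefore described as one pool. It is not stated that one person keeps the same family throughout. The passage on the calls speaks of research staff, and the word *same* in the post-test sentence refers back to baseline.

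3. **Who learns the arm.** The exception is in the passive voice and names nobody. It follows directly on sentences about keeping assessors blind, so the assessor is the natural reading, but that is an inference. Programme coordinators and facilitators deliver the intervention and so know allocation already.

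4. **What triggers it.** The checklist has 3 physical or medical + 3 behavioural + 1 emotional + 5 daily-life items = 12. Behavioural items are 3 of 12 and the rest 9 of 12. These are shares of items, not of expected events. An event may concern the child or the caregiver. The word *serious* stands in brackets, so it is unclear whether every adverse event triggers unblinding or only serious ones.

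5. **Which measures are exposed.**
   - The PDR is listed under the primary outcome and is taken by telephone in the same calls as the adverse events, so it is exposed at later calls.
   - The MINI-KID-P diagnosis of ODD or CD, also listed under the primary outcome, comes from a structured interview and is exposed at post-test and follow-up.
   - The CBCL aggression score is parent-reported. In person the parent enters the answers on a tablet, and parents are told their arm after baseline. Assessor blinding protects this score only to a limited extent.
   - Under pandemic restrictions interviews move to the telephone, where the article accepts that parents cannot answer privately. That narrows the protection of self-entry.

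6. **Safeguards.** Assessors ask parents at post-test and follow-up not to disclose their group. Nothing says what happens to later interviews once the adverse-event exception has been used.

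**The case against.** The strongest reply is that a general rule followed by a declared exception is not a contradiction, and that *Procedure* merely restates the rule. Who takes over after unblinding is also the kind of operational detail that an article leaves to the full protocol. This stands in part: silence about reassignment alone would be no finding. But the article prints the rule, the exception and the staffing. Followed as printed, they do not guarantee a blinded post-test in families where the exception was used.

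Three stronger readings are tempting and are not supported.

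- **That blinding is lost selectively in families whose child has worsened.** Nine of the 12 items are not behavioural, caregiver events count, and if only serious events qualify, few behavioural reports would trigger unblinding.
- **That relatedness is judged with the arm known.** The article says the research teams will try to classify relatedness from the parent's report. It does not say whether they know the arm when they do so.
- **That the bias can be put at a definite share of the planned effect.** Suppose 5% to 20% of families were unblinded and the arm contrast in them shifted by 0.2 SD. Then 704 × 0.05 = 35 to 704 × 0.20 = 141 families would be affected. The overall shift would be 0.05 × 0.2 = 0.01 to 0.20 × 0.2 = 0.04 SD, or 4% to 16% of d = .25. Neither input is in the document, a 0.2 SD assessor effect on a parent-reported score is not justified, and an SD shift does not carry over to the binary MINI-KID-P result. These figures should not be used as an estimate.

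**Conclusion.** The point holds in limited form. The article's blinding statements do not fit its adverse-event exception, and the exception can remove assessor blinding before later outcome interviews on a trigger that partly overlaps the primary outcome construct. This rests on two inferences: that the assessor is the person unblinded, and that callers and later interviewers overlap. The text makes both likely but states neither.

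The later PDR calls, the MINI-KID-P and telephone interviews are the most exposed. The effect on CBCL aggression is likely small. The total size is unknown, and it depends heavily on whether the bracketed word limits the trigger to serious events. The point does not undermine the design, but it is worth correcting because a procedure that keeps the assessor blind is available at little cost.

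**What to change.** Reconcile the three sections as follows.

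- State who may be unblinded and whether all or only serious adverse events qualify.
- Have the data assessor record the event without asking for or being told the arm, and pass it to programme staff who already know allocation for anything that requires it.
- Classify relatedness first without the arm where possible.
- If an assessor does learn the arm, log it and give that family's remaining interviews to another assessor on the existing team. According to *Trial status*, post-assessments finished on September 24, 2021, so this now concerns the 12-month follow-up.
- For the calls and post-tests already done, establish from existing records which were conducted unblinded, and report the number by arm.
- Keep every family in the intention-to-treat analysis. An analysis that leaves out unblinded interviews may be shown as supportive only. It selects on an event after randomisation that may be related to the outcome, and so can introduce bias of its own.

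The cost is a few sentences of procedure, a log, and some rescheduling within the existing team. The article does not give team size, so each site should confirm that a second assessor is available.

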### Procedure

The interviews will be conducted in-person or over the telephone by trained data assessors, with experience in conducting field research with semi-structured interviews. In order to be assessed and further take part in the study, primary and consenting secondary caregivers will give verbal or signed consents to data assessors. If the interviews are conducted over the phone, the data assesors will send the *Information Sheet and the Informed Consent* (Appendix 1) to the participant ahead of time. During the interview, they will go over the Information Sheet with the participant and then present the informed consent. If the participant agrees verbally with each item from the informed consent, the data assessors will fill in the respective form, write the participant’s name and sign it with the data assessors’ name. For in-person interviews, the same procedure will apply, but the participant will fill in and sign the informed consent with their own names.

Data from the measurement points (pre-test, periodic, post-test, and follow-up) will be collected by using Open Data Kit (ODK), installed on individual tablets. This software was used in the previous two study phases and proved to be very well accepted and easy to adapt to the languages of data collection (i.e. Albanian, Romanian, Russian, Macedonian).

The interview format will follow a “computer-assisted self-interviewing” format (CASI), in which the interviewer will read out the questions whilst the participants select their answers on the tablet, with support where needed. For sensitive questions referring to intimate partner violence, child maltreatment, and parents’ history of abuse during childhood, we will employ an audio-CASI interviewing method, which allows participants to listen to the recorded question and answer privately on the tablet. Alternatively, parents can read the question and answer the items by themselves on the tablet.

If restrictions due to the COVID-19 pandemic will not allow in-person assessments, interviews will be completed over the phone. Because parents will not have the option to answer items privately over the phone, the sensitive items will not be administered during phone assessments. If restrictions due to the COVID-19 pandemic do not allow in-person assessments at post-test and follow-up assessment, parts of the assessment will also be offered online (the sensitive items) so that parents may answer the sensitive items privately via the online survey. If sensitive baseline measures (parents’ own history of child maltreatment) cannot be administered during the pre-assessment (due to phone assessment mode), they will be assessed at the next possible assessment point (e.g. post-assessment).

Approximately 4 months after the pre-assessment, post-test assessments will be carried out with the help of the same research assistants, blinded to the study conditions (planned for May / June 2021). Around 12 months after pre-assessments, we plan to carry out the follow-up assessment (December 2021–February 2022).

Three repeated ratings of child and parent behaviour in the past 24 h will be assessed over the phone between pre-intervention and post-assessment. For the PLH-YC group, after the 1st, 3rd, and 5th session (lecture: after the lecture, 2 weeks and 4 weeks later), research staff will phone participants in order to monitor the adverse events and to assess parent and child behaviour, see Fig. 1Appendix 2—Study flowchart, for a tentative timeline and Additional file 1—Schedule of enrolment, interventions and assessments (SPIRIT Figure).

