##### Primary and secondary outcome analyses

Data will be analysed using an intention-to-treat approach, in line with the study protocol and with good practice in RCTs [70]. Missing data will be handled using either multiple imputation or Full Information Maximum Likelihood (FIML) method [71].

The primary analysis will consist of testing comparatively the magnitude of change in child aggresive behaviour, in the control vs. PLH-YC participants, at post-test and follow-up. Identical analyses will be run for the secondary outcomes (i.e. child internalising problems, dysfunctional parenting strategies, positive parenting, daily reports of effective parenting behaviour, child maltreatment, parental mental health, IPV, couple satisfaction, parenting stress, quality of parent-child relationship, and child ’s quality of life). The main analyses will involve testing pre-post or pre-follow-up differences controlling for pre-intervention levels whilst accounting for covariates. Maximum likelihood estimation with robust statistics will be used with Mplus 8.2 software to account for non-normal distributions in measures and also apply a FIML framework for handling missing data at post- or follow-up. The models will be further tested using latent growth curve models adjusting for country and pre-assessment levels of the outcome variables (e.g. age as a time-invariant covariate). Indirect effect models will be tested in a structural equation framework and include participation rate and fidelity as mediators for the PLH-YC group and enrolment rate as the mediator across groups. In additional analyses, we will also model the effects of participation (i.e., attendance). This will be analysed with Complier Average Cause Effect models that estimate the magnitude of the paths based on the baseline scores in predictors (e.g. family adversity) and actual participation [72]. Further clustering will be within groups (facilitators) and included in subsequent analyses as needed. The analyses for MINI-KID ODD/CD positive screen will be conducted with logistical regression models due to the categorical nature of the data. Depending on the distributions and on other descriptive indicators, Bayesian analyses will be used as deemed appropriate.

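### Phone-baseline families have no observed pre-intervention value for child maltreatment or partner violence, although change from baseline and a baseline predictor are to be analysed

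*Protocol article*

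**What the plan says.** All of this is in the protocol article.

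- **Which items are sensitive (Procedure).** A private audio method is used in person "For sensitive questions referring to intimate partner violence, child maltreatment, and parents’ history of abuse during childhood".
- **Phone interviews (Procedure).** If COVID-19 restrictions rule out meeting in person, the interview is by phone. "Because parents will not have the option to answer items privately over the phone, the sensitive items will not be administered during phone assessments".
- **Private online route (Procedure).** It applies if restrictions "do not allow in-person assessments at post-test and follow-up assessment, parts of the assessment will also be offered online (the sensitive items"). No such route is given for the pre-assessment.
- **Catch-up rule (Procedure).** It opens "If sensitive baseline measures (parents’ own history of child maltreatment) cannot be administered during the pre-assessment (due to phone assessment mode") and moves those items to the next possible assessment. Only the parents' own history is named.
- **Analysis (Primary and secondary outcome analyses).** "The main analyses will involve testing pre-post or pre-follow-up differences controlling for pre-intervention levels whilst accounting for covariates". The same analyses are to be run for the secondary outcomes, whose list includes child maltreatment and intimate partner violence.
- **Missing data (same section).** A general sentence provides for multiple imputation or FIML without naming a wave. A later sentence on the main models says they will "apply a FIML framework for handling missing data at post- or follow-up".
- **Hypotheses (Overview and aims).** Secondary outcomes are to show change from before the intervention to follow-up. Baseline partner violence is one component of the family adversity expected to lower enrolment and participation.

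**The concern.** The plan recognises that sensitive questions cannot be asked privately by phone, and it has a solution for the two later waves. It does not apply that solution at baseline, the one wave where the loss cannot be made good. A parent's own childhood history is a fixed past exposure and can be asked later. Current maltreatment and current partner violence cannot: a first value at post-test comes after randomisation and after treatment.

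At stake are three things for the phone-baseline families: observed change on two secondary outcomes, the precision gained from baseline adjustment on those outcomes, and the test of baseline partner violence as a predictor. Without further provision, that test rests on families interviewed in person, a subset selected by restriction period and area.

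**Working it through.** There is no plan figure to reproduce. The point is a comparison of what is collected with what is analysed, followed by an illustration of size.

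**Collection against use**

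| Construct | Asked at a phone baseline? | Caught up later as a baseline value? | Baseline value used for |
|---|---|---|---|
| Parents' own abuse history | No | Yes, at the next possible assessment | Background exposure |
| Child maltreatment | No | No | Change and baseline adjustment |
| Partner violence | No | No | Change, baseline adjustment, predictor of enrolment and participation |

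**Size: inputs**

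- From Sample size calculation: 864 recruited, 704 analysed (352 per arm), d = .25, two-sided alpha .05. The plan sets d and 704 for the primary outcomes; they are borrowed here for illustration only.
- Assumed: share p of phone baselines, which the document does not give, and pre-post correlation r = .5.

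**Formulas**

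Relative to a participant without a baseline, one with a baseline contributes information 1/(1 − r²). The effective number per arm is then

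- everyone kept: n = 352 × [(1 − p)/(1 − r²) + p]
- complete cases only: n = 352 × (1 − p)/(1 − r²)

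and power = Φ(.25 × √(n/2) − 1.96).

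Example, p = .50: everyone kept, n = 352 × (.50/.75 + .50) = 411, so power = Φ(3.58 − 1.96) = .95. Complete cases, n = 352 × .50/.75 = 235, so power = Φ(2.71 − 1.96) = .77.

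| p | Baseline observed, of 864 | Complete cases, of 704 | Power, everyone kept | Power, complete cases |
|---|---|---|---|---|
| 0 | 864 | 704 | .97 | .97 |
| .25 | 648 | 528 | .96 | .91 |
| .50 | 432 | 352 | .95 | .77 |
| .75 | 216 | 176 | .93 | .48 |
| 1 | 0 | 0 | .91 | no analysis |

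Sensitivity to r at p = .50: for r from .3 to .7, power runs from .93 to .98 with everyone kept and from .69 to .91 with complete cases.

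The between-arm contrast at later waves therefore loses little if all families stay in. No analysis supplies an observed change score or an observed baseline partner-violence value for a phone-baseline family.

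**The case against.** The strongest reply is that the missing-data plan already covers this. The general sentence on multiple imputation or FIML is not tied to a wave, and multiple imputation can handle a missing baseline covariate. Growth models are also planned; where the pre-assessment is one of the modelled waves, a family lacking it can stay in under FIML. Whether the baseline enters as a conditioning covariate or as a modelled variable is normally settled in a SAP, which is not shown. This stands, and it limits the point.

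A reader might infer from the later FIML sentence, which mentions only post-test and follow-up, that phone-baseline families drop out and that the intention-to-treat comparison shrinks to in-person families. The document does not support that: it nowhere plans listwise deletion, and the general sentence points the other way. A reader might also compute an unadjusted complete-case comparison of 528/352/176 families and report power of 82/65/38%. Those figures assume both case deletion and no baseline adjustment, and neither is the plan.

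Nor is there bias in the randomised contrast. Allocation follows the baseline interview, so its mode cannot depend on arm.

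The scope is also limited. The primary outcome measures are not among the sensitive items, and partner violence is one of several adversity components.

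What the reply does not remove is the collection rule. Followed as written, it leaves two outcomes without an observed baseline for everyone interviewed by phone. Imputation would have to borrow that baseline from in-person families; if a whole country were interviewed by phone, it would have to borrow from the other countries.

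**Conclusion.** The point holds in a limited form. The stated procedure loses, irrecoverably, the pre-intervention values of child maltreatment and partner violence for phone-baseline families, while the stated analyses and one predictor hypothesis use those values. The harm falls on observed change, baseline adjustment and the partner-violence predictor test, and not on the validity of the randomised comparison at post-test or follow-up.

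The size depends on a phone share that the document does not give. Trial status dates recruitment from 7 December 2020 to 17 May 2021, under a plan that anticipates pandemic restrictions, so a large share is plausible but not shown. Under the assumptions above, the power cost is small if all families are kept and substantial only if the analysis falls back on complete cases. This merits correction, but it concerns secondary outcomes and leaves the primary analysis untouched.

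**What to change.** **In the design.** Offer the same private online survey of sensitive items at the pre-assessment, completed before randomisation. It is already planned for the later waves, so the cost is small. The downside is that some parents will not complete it. Trial status reports recruitment as complete, so this can no longer help families already enrolled.

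**For families enrolled without it.** Only analysis wording is needed:

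- Compare the arms on post-test and follow-up levels of child maltreatment and partner violence, with all randomised families kept.
- Model the baseline score jointly with the outcomes, or use a missing-baseline indicator. Either is sound here because mode is set before allocation.
- Include baseline interview mode as a covariate.
- Report the baseline partner-violence predictor analysis as restricted to families interviewed in person at baseline.

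This recovers the between-arm comparison. It does not recover observed change or the predictor values for phone-baseline families.
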